## Abstract

**Background:**

The objective of this study is to evaluate the effectiveness of pharmacist intervention in improving disease knowledge, adherence to treatment, health-related quality of life (HRQoL) and direct cost of treatment. The study also documents patient satisfaction with pharmacist counselling as a quality control measure.

**Methods/design:**

This is a randomized, single-blind, two-arm, controlled trial in patients with rheumatoid arthritis visiting outpatient rheumatology clinics in Karachi, Pakistan. We will enroll patients with established diagnosis of rheumatoid arthritis over 3 months. The patients would be randomized through a computer-generated list into the control group, i.e., usual care or into the intervention group, i.e., pharmaceutical care, in a ratio of 1:1, after providing signed written consent. The study will take place in two patient-visits over the course of 3 months. Patients in the intervention group would receive intervention from the pharmacist while those in the control group will receive usual care. Primary outcomes include change in mean score from baseline (week 0) and at follow up (week 12) in disease knowledge, adherence to medications and rehabilitation/physical therapy. The secondary outcomes include change in the mean direct cost of treatment, HRQoL and patient satisfaction with pharmacist counselling.

**Discussion:**

This is a novel study that evaluates the role of the pharmacist in improving treatment outcomes in patients with rheumatoid arthritis. The results of this trial could set the foundation for future delivery of care for this patient population in Pakistan. The results of this trial would be published in a peer-reviewed journal.

**Trial registration:**

ClinicalTrials.gov, NCT03827148. Registered on February 2019.

**Electronic supplementary material:**

The online version of this article (10.1186/s13063-019-3540-z) contains supplementary material, which is available to authorized users.

## Background

Rheumatoid arthritis (RA) is a chronic inflammatory disease that mainly affects the joints and results in pain, swelling and decreased mobility. The disease leads to joint deformity and disability over time. The disease ranks third after osteoarthritis and gout as the major cause of disability and affects roughly 1% of the global population. Reduced mobility results in decreased productivity among patients and further worsens their quality of life [1]. While pharmacological treatment may be essential in managing the acute flares and episodic pain associated with the disease, self-care and home-based management of RA is another important area of care that patients need to incorporate to effectively manage RA.

Several studies have reported that self-care in RA effectively reduces acute flares [2, 3]. This could be done through patient education and counselling. Pharmacists provide pharmaceutical care that incorporates these areas of care. Pharmaceutical care is an individualized patient-centric health service delivered by pharmacists that incorporates, but is not limited to, disease education, therapy management, self-care and self-management of disease, therapy and motivational guidance.

Evidence from several randomized trials indicate that pharmacist-driven patient counselling, consultation, disease education and advice, as well as telephonic intervention, have improved patients’ self-care. Educating patients about managing RA empowers them in understanding signs and symptoms of disease and devising ways to reduce or limit aggravating factors. A randomized trial conducted by Petkova that involved a community, pharmacy-based, patient education program and demonstrated improved treatment outcomes in patients with RA [4]. Moreover, Mary and colleagues demonstrated a positive effect of a mobile phone short message service on medication adherence in patients with RA [5]. A systematic literature review by Leville and colleagues highlighted the role of the pharmacist as an adviser on issues related to medication management. The intervention performed by pharmacists has shown improvement in patients’ adherence to medication not only in rheumatological conditions but also in other chronic illnesses [6, 1]. Another randomized controlled trial (RCT) by Clifford and colleagues reported a significant drop in non-adherence to medication and in the incidence of medication-related problems after a 4-week follow up. This improvement was reported in patients with RA who had telephone intervention delivered by the pharmacist [7]. Moreover, Stockl and colleagues reported improved adherence to medication in patients with RA who had telephone consultations with the pharmacist [8].

Recent evidence that evaluates the pharmacist’s role in managing RA is scant. Moreover, to date there has been no study conducted in Pakistan to evaluate this issue. One has to look into the role and scope of pharmacy practice in Pakistan’s healthcare system to understand the need for such studies. Pharmacy services are still in the developmental phase and have not attained the level of healthcare delivery as in many economically developed and developing countries. Pharmacists are not involved in patient care to a great extent and are mostly associated with dispensing medicines. There are several barriers to the delivery of pharmaceutical care services in Pakistan [9]. The recognition of pharmacists as members of allied health teams who are involved in direct patient care is limited and is still debated. Studies have called for evaluation of the benefits of pharmacist inclusion in direct patient care [10]. Cardiovascular and endocrine illnesses are the leading cause of deaths in the Pakistani population. Studies have been conducted to report the impact of pharmacist-led care in patients with endocrine and cardiovascular illnesses [11–13].

Musculoskeletal illnesses are a major contributor to the individual’s decreased productivity, economic burden and mobility. Unlike other noncommunicable diseases, these illnesses may not result in death. However, they are the most common cause of persistent pain and impaired function [14]. They significantly decrease a person’s mobility, productivity and quality of life [15, 16]. The most common musculoskeletal illnesses are osteoarthritis, RA and osteoporosis [14, 16]. Data from the Institute of Health Metrics and Evaluation show that the prevalence of RA in Pakistan is 0.22% (0.22–0.25%). However, the figures for years lived with disability (YLDs) are high, i.e., 28.59 years (19.12–39.02), and for disease-adjusted life years (DALYs) were 39.64 years (28.84–51.75). These figures further rise to 0.92 (0.52–1.69) deaths due to RA, 40.12 (26.73–54.81) YLDs and 56.67 (40.22–75.92) DALYs in female patients with RA. All figures were reported out of 100,000 patients [17].

Since disease prevalence has increased in Pakistan of late and mainly affects middle-aged individuals, it is expected to affect their productivity, employability and income. This would worsen their health-related quality of life and adds to the economic burden of this disease on society. Therefore, there is a need to evaluate the impact of pharmaceutical-care-based educational intervention delivered by the pharmacist on treatment outcomes in Pakistani patients with RA.

### Objectives

The primary objective of the study is to evaluate the effectiveness of a multifactorial educational intervention on patient knowledge of RA and adherence to treatment. This intervention would be provided by a pharmacist. The secondary objectives are to assess the impact of the intervention on the cost of treatment, quality of life and patient satisfaction.

### Trial design

This trial is designed as a randomized, single-blind, parallel group trial. It has two arms, i.e., a control or “usual care” arm and an intervention or “pharmaceutical care” arm. Patients would be recruited and randomly assigned to either of the two arms using a computer-generated list and the patients’ medical record numbers. The allocation ratio would be 1:1. The trial has been designed as per the Standard Protocol Items: Recommendations for Interventional Trials (SPIRIT) and Template for Intervention, Description and Replication (TIDieR) checklists which are available as Additional files 1 and 2.

## Methods/design

### Design and setting

This study is a randomized, single-blind, parallel trial. The patients who participate in this study after providing signed consent would be randomly assigned to either the control group (CG), i.e., usual care, or intervention group (IG), i.e., pharmaceutical care. The allocation ratio will be 1:1. The participants in the IG would receive an educational intervention delivered by the pharmacist and provided with disease education literature. The participants in the CG would receive usual care without pharmacist intervention. The usual care in Pakistan’s healthcare system encompasses an appointment with a physician, which does not include pharmaceutical care. Usually, a pharmacist is limited to dispensing medicines to patients.

### Recruitment strategy

The patients will be recruited from the rheumatology departments at three tertiary care hospitals located in city of Karachi, Pakistan. Patients will be recruited through an advertisement displayed at the reception counters. The recruitment advertisement is still ongoing. A study officer would administer the consent form, which is available in both the English and Urdu languages, and enroll consenting patients in the study. The list of study sites is available as Additional file 3.

### Study plan

The process will start after patients attend the study explanation session and consent to participate. The patients who refuse to participate will be provided regular hospital care. Patients who consent to participate will sign the patient consent form and will be screened for eligibility. Ineligible patients will be excluded from the study and given regular hospital care. Eligible patients will be randomized by computer software into the IG or CG. Patients’ baseline data will be recorded. Enrolled patients’ demographic data will be documented at baseline. Patients will have their anthropometric measurements, i.e., weight, height, etc. noted in addition to their socio-demographic data. Moreover, the patients will be assessed for the outcome measures. The patients randomized into the IG will be provided pharmacist intervention. At the follow-up appointment, i.e., after 3 months (week 12) from baseline (week 0), the same data will be recorded from patients in both treatment groups.

Attention is paid to achieving high patient-retention rates by comprehensively briefing the patients and answering their queries. In the case of loss to follow up, the rheumatologist and the hospital’s front desk staff will establish contact with the patient, try to convince them to participate and if not, document the reason for leaving the study. The whole study will encompass two visits in due course (Fig. 1).

**Fig. 1 Fig1:**
[figure not shown]
Study flow diagram

### Participants

#### Inclusion criteria

The patients who meet the following criteria will be invited to participate in our study:Patients suffering from RA diagnosed according to the 2010 American College of Rheumatology (ACR)/European League Against Rheumatism (EULAR) criteriaPatients diagnosed with RA based on the aforementioned criteria for at least 3 months prior to study invitationPatients older than 18 yearsPatients visiting outpatient clinics only

Patients attend a study explanation session and provide written consent to participate before enrolling in the study.

#### Exclusion criteria

Patients are excluded from the study based on the following conditions:Musculoskeletal illnesses other than RARecent history of surgery or planned surgery for RAMore than three comorbiditiesAbnormal laboratory measurements and receiving treatment for liver or kidney diseaseSevere infection and/or completed a course of antibiotics in the last weekAdvanced cardiovascular disease, severe allergies or a rare diseaseCurrent participation or participation within the last 3 months in another clinical trialPregnancy, planning a pregnancy, breast feeding or other gynecological issues in women

### Randomization and allocation concealment

Patients will be randomly allocated to one of the two treatment groups using a randomization ratio of 1:1. The technique used will be simple randomization using a computer-generated list. The participants’ medical record numbers will be entered into the hospital’s software and a list of appointments will be generated with patients designated into the CG or the IG.

Allocation will be automatically concealed through the computer-generated list, which automatically allocates a clinic room number. For instance, if the computer enrolls a patient into the IG, it generates the appointment slip with a clinic room number in which a pharmacist will provide the intervention and vice versa. There are two room numbers, i.e., 1 = without pharmacist intervention and 2 = with pharmacist intervention. The patients and data collectors will be unaware of this number scheme. Patients in the CG will go to clinic room 1 and have their consultation with rheumatologist. The pharmacist will not provide the intervention. Before consultation, the patients will go to a consultation room where a data collector will wait with a data file printed on yellow-colored paper. If the computer enrolls a patient into the IG, the appointment slip will be printed with clinic room number 2. Patients in the IG will go to that clinic room where the rheumatologist and a pharmacist await them. The patients will undergo the intervention after consultation with the rheumatologist. Similarly, before the intervention, patients will enter a consultation room where the data collector will wait with a patient data file printed on white paper. The data collector and pharmacist will be unaware of the color scheme. Therefore, the pharmacist will be unaware of outcome assessment.

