### Statistical analysis

The statistical analysis will be conducted by a statistician who will be blinded to patient-group allocation. The analysis will be carried out using SPSS version 22 (IBM SPSS, Armonk, NY, USA). The analysis will consist of a per-protocol set that includes participants who have completed the study as per the defined protocol. The significance level will be set at 5% and a two-tailed test will be used. Continuous data will be descriptively analysed using the Mann-Whitney U test, while the chi-square test will be used to analyze categorical variables by comparing them in the two groups at the same time point. Confirmatory analysis will be carried out using the Wilcoxon signed-rank test to analyze differences in the mean values for disease knowledge, adherence to treatment and medications and the cost of treatment after 3 months, i.e., baseline within-subject analysis. Multinomial logistic regression will be used to interpret the odds ratios for the secondary outcome, i.e., patient satisfaction with pharmacist counselling. There will be no interim data analysis.

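### The named between-arm tests ignore hospital although patients come from three sites under simple randomisation; this costs some precision but causes no bias

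*Protocol article*

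**What the plan says.** Under Recruitment strategy, the protocol article states: "The patients will be recruited from the rheumatology departments at three tertiary care hospitals located in city of Karachi, Pakistan".

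Under Randomization and allocation concealment it gives the ratio, "Patients will be randomly allocated to one of the two treatment groups using a randomization ratio of 1:1", and the method, "The technique used will be simple randomization using a computer-generated list". It adds that patients' "medical record numbers will be entered into the hospital’s software". It does not say whether there is one list for the trial or one per hospital, and it names no stratification factor or blocking.

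Under Statistical analysis, two tests compare the arms. For continuous data: "Continuous data will be descriptively analysed using the Mann-Whitney U test". For categorical data: "the chi-square test will be used to analyze categorical variables by comparing them in the two groups at the same time point". Neither is given a hospital stratum or covariate. The test labelled confirmatory is a within-patient one: "Confirmatory analysis will be carried out using the Wilcoxon signed-rank test". Multinomial logistic regression is reserved for patient satisfaction, which the Outcomes section evaluates in the intervention group only.

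**The concern.** Hospital is known for every patient and could plausibly be related to several outcomes. Direct cost is built from rheumatologist appointments, follow-ups, medicines and physical therapy, whose prices may differ by hospital. Adherence to physical therapy may depend on what each hospital offers. Simple randomisation does not force balance within a hospital, and an unstratified Mann-Whitney or chi-square test has no place for a covariate. Variation between hospitals therefore goes into the error of the arm comparison. At stake is precision that the trial could recover from data it already holds.

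**Working it through.** **Inputs from the protocol article.** Three hospitals; 1:1 simple randomisation; 619 patients in total with 20% drop-out expected (Sample size); a per-protocol analysis set (Statistical analysis). Completers: 619 × 0.8 ≈ 495.

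**Assumptions, because the article gives no values.** Equal hospital sizes, so 619/3 ≈ 206 randomised and 495/3 = 165 completing per hospital. Hospital share of outcome variance, R: 0 to 30%. True effect in the simulation: 0.25 SD.

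**The plan's own figure.** The only sample figure is 619, and hospital does not enter it. Its stated inputs (16% v 9%, two-sided 5%, 80% power) give n per arm = [1.96√(2 × 0.125 × 0.875) + 0.8416√(0.16 × 0.84 + 0.09 × 0.91)]² / 0.07² ≈ 349.2, rounded up to 350. That is 700 evaluable, or 700/0.8 = 875 with drop-out. So 619 does not reproduce. This is a separate matter; 619 is used below only to set hospital sizes.

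**Imbalance that simple randomisation allows (95% ranges).**
- Difference between arms in one hospital's share of patients: 1.96 × √[(1/3)(2/3) × 2/309.5] = 0.074, or 7.4 percentage points either way.
- Intervention patients in a hospital of 206: 103 ± 1.96 × √206.3/2 = 103 ± 14, or 89 to 117.
- Among 165 completers: 0.5 ± 1.96 × 0.5/√165, or 42% to 58% in the intervention arm.

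**What this does to the outcome.** The arm difference has standard error of about 2/√495 = 0.090 SD. The hospital part of it is √R × 2/√495. Removing it multiplies the standard error by √(1 − R), which is worth 1/(1 − R) times the patients. Chance imbalance is the route by which hospital variance enters the error, so the two are one effect and are counted once.

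The last two columns come from a simulation (3,000 trials per setting, 3 × 165 patients, normally distributed outcome) comparing the unstratified Mann-Whitney test with a linear model that includes hospital.

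| R | Cut in SE | Equivalent extra patients | SD of chance shift | Power, unstratified | Power, hospital in model |
|---|---|---|---|---|---|
| 0 | 0% | 0% | 0 | 76.9% | 79.3% |
| 5% | 2.5% | 5% | 0.020 SD | 78.1% | 82.0% |
| 10% | 5.1% | 11% | 0.028 SD | 77.1% | 82.4% |
| 20% | 10.6% | 25% | 0.040 SD | 76.9% | 87.9% |
| 30% | 16.3% | 43% | 0.049 SD | 76.1% | 91.3% |

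At R = 0 the model already leads by 79.3 − 76.9 = 2.4 points. Hospital cannot explain that gap; it reflects a linear model against a rank test on normal data. About 2 points should therefore be discounted from each row's gap.

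**Validity of the unstratified test.** Across R from 0 to 30%, its simulated bias was within 0.003 SD of zero and its type I error was 3.7% to 5.2%. Monte Carlo error is about √(0.05 × 0.95/3000) = 0.4 points, so there is no sign of inflation.

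**The case against.** The strongest case against the point is that nothing here is an error. Patients are randomised individually, and both arms are described as running side by side in two clinic rooms, so hospital is unrelated to arm in expectation. A reader might infer that hospital confounds the comparison; the design and the simulation show that it does not. That part of the objection stands in full.

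The size also rests on an assumed variance share. The sites are all tertiary departments in one city, and the Abstract and Discussion define the primary outcomes and cost as changes from baseline, so stable hospital levels would largely subtract out. This stands too, with one limit: Statistical analysis does not say whether the Mann-Whitney test is applied to changes or to week-12 values, and on week-12 values the hospital levels would remain.

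Covariate adjustment is often left to an analysis plan, and none is shown. This stands only in part. The article does not leave the method open: it names tests that cannot take a hospital term, so a later plan would have to replace them.

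Three further readings are tempting, and the article does not support them:
- That everything rests on one pooled test. Several tests are listed, the Mann-Whitney is called descriptive, and the confirmatory one does not compare the arms. That last fault is separate and more serious, and hospital stratification does not cure it.
- That pharmacist differences are ignored. The Intervention section plans mixed models with random intercepts for pharmacists, though for implementation. Pharmacists act only in the intervention arm, so hospital strata would not remove that clustering.
- That the allocation list should now be blocked by hospital. Recruitment strategy says advertising is ongoing, but Trial status says the trial is not recruiting and that final results are being analysed, so a change to the list would come too late.

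**Conclusion.** The point holds as a modest loss of precision. The named between-arm tests leave hospital variance in the error; they are neither biased nor liberal. With a hospital share of 5% to 20%, using hospital would cut the standard error by about 3% to 11%. With a share near zero it would make almost no difference. These shares are assumptions, as are the equal hospital sizes. Direct cost and physical-therapy adherence are where a gain is most plausible; outcomes analysed as change from baseline would gain less. Patient satisfaction is unaffected because it has no control-arm comparison.

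**What to change.** State that the between-arm comparisons are stratified by hospital: the van Elteren test in place of Mann-Whitney, and Cochran-Mantel-Haenszel in place of the plain chi-square. Alternatively, include hospital as a fixed factor in a between-arm model. Specify and date this before the statistician, who is described as blinded, learns the group codes, and keep the unstratified tests as a sensitivity analysis. If the codes have already been opened, the stratified results should be labelled post hoc.

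No new data are needed. The cost is about two degrees of freedom (three hospitals less one) and a late change to the analysis that must be documented and reported. The team should check that SPSS version 22, the package named, can run the van Elteren test; if it cannot, the fixed-factor model is the alternative.

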### Blinding

The investigators, data collectors, study observers, data entry operators and data analysis statistician will be blinded to the allocation. The patients will not be blinded to the pharmacists; however, they will be blinded to the intervention. The data collector will not know if the patient belongs to the IG or CG. The pharmacist will be blinded to the outcome assessment so that there will be less likelihood of intervention bias. The blinding scheme is shown in Table 1.

**Table 1 Tab1:** Blinding scheme

Stake holders	Allocation scheme	Intervention allocation room	Pharmacist intervention	Data form color code	Outcome assessment	Data analysis
Study observers	A	NA	A	A	A	A
Study officer	NA	NA	NA	NA	NA	NA
Patients	NA	NA	NA	NA	NA	NA
Pharmacists	NA	NA	A	NA	NA	NA
Rheumatologists	NA	NA	A	NA	NA	NA
Data collectors	NA	NA	NA	NA	NA	NA
Data analysis technicians	NA	NA	NA	NA	NA	A

*A* Aware, *NA* Not aware

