### Data management

The data collection process will be conducted as per the defined protocol and standard operating procedures approved by the committee, to ensure genuine and good quality data. The patients will be given a study explanation session and after giving their consent, will be randomized and have their baseline data documented. After consultation, they will be informed about their follow-up visiting schedules. Patients with RA are usually given a follow-up appointment after 3 months. In addition, they are reminded about their visits via text reminders and followed by telephone calls if absent on the day of the appointment. The data will be collected by an independent assessor who will be blinded to the study objectives and intervention. After completion of the study, a data entry officer will enter the data into the software. This will be checked/validated by another person by comparison with the original patient data file. Any mistakes made during data entry will be rectified at this point.

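### Arm-coloured forms waiting with the data collector either tie collectors to an arm or give a collector who serves both arms a two-group code; the article does not say which

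*Protocol article*

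**What the plan says.** In the Protocol article, Randomization and allocation concealment describes the data-collection step separately for each arm. Control patients first go to "a consultation room where a data collector will wait with a data file printed on yellow-colored paper". For the intervention arm, "patients will enter a consultation room where the data collector will wait with a patient data file printed on white paper". Two statements there are meant to protect blinding: "The patients and data collectors will be unaware of this number scheme" (the clinic room numbers) and "The data collector and pharmacist will be unaware of the color scheme".

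Blinding adds that "The data collector will not know if the patient belongs to the IG or CG", and Table 1 there marks data collectors as not aware in every column. Data management says "The data will be collected by an independent assessor who will be blinded to the study objectives and intervention". Under Recruitment strategy, patients are "recruited from the rheumatology departments at three tertiary care hospitals".

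The article does not give the number of collectors or say whether each serves one arm or both. Nor does it say whether the same collector sees a patient at weeks 0 and 12, whether the colours are kept at week 12, or whether the scales are read out or completed by the patient. Under Statistical analysis, the tests between arms (Mann-Whitney, chi-square) compare the groups at one time point, and the test called confirmatory (Wilcoxon signed-rank) is within-subject. The only random intercepts, under Intervention, are for pharmacists.

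**The concern.** The colour is in the collector's hand before the patient enters, and it follows the arm. A collector who knows neither the room code nor the colour code, yet always has the right form ready, is most easily explained by one collector or one room per colour. The person recording the outcome would then coincide with the arm.

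That is a separate problem from blinding. A perfectly blinded collector who sees only one arm still brings a personal way of explaining items and accepting answers, and this enters that arm's scores. In a comparison of the arms at one time point it looks like a treatment effect, and a larger sample only makes it easier to declare significant.

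If instead one collector handles both colours, the confounding goes but patients arrive visibly sorted into two groups. If the colours are kept at week 12, one patient who mentions the pharmacist reveals the meaning of that colour for everyone else.

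**Working it through.** The article has no figure of its own on this point, so there is none to reproduce. The calculation below is an illustration; the interviewer shift, the intra-collector correlation and the number of collectors are assumptions.

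**Inputs.** Total sample 619 and drop-out 20% (Sample size, taken as printed), allocation 1:1, two-sided 5% level. Evaluable per arm: 619 × 0.8 / 2 = 247.6, taken as n = 247.

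**1. Fixed shift, one collector per arm, no true effect.** Let d be the difference between the two collectors in SD units. A normal approximation stands in for the rank test.

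False-positive rate = P(|Z + d/√(2/n)| > 1.96), with √(2/247) = 0.0900.

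| d (SD) | d/√(2/n) | False-positive rate |
|---|---|---|
| 0 | 0 | 5% |
| 0.05 | 0.56 | 8.6% |
| 0.10 | 1.11 | 19.9% |
| 0.15 | 1.67 | 38.5% |
| 0.20 | 2.22 | 60.4% |

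**2. Several collectors per arm.** Treat collectors as random, k per arm, with intra-collector correlation ρ. The variance of the difference is 2[(1−ρ)/n + ρ/k] instead of 2/n, here with n = 247.6. The true error rate is 2[1 − Φ(1.96 × √((1/n) / ((1−ρ)/n + ρ/k)))].

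| ρ | k = 1 | k = 3 (one per hospital and arm) |
|---|---|---|
| 0.005 | 19% | 10% |
| 0.01 | 29% | 15% |
| 0.02 | 42% | 23% |
| 0.05 | 59% | 38% |

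More collectors per arm reduce the inflation but do not remove it.

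**3. Change from baseline.** Suppose the same collector sees a patient at both visits and adds a constant s. Then (week 12 + s) − (week 0 + s) = week 12 − week 0. The shift cancels, and a between-arm test of change keeps its 5% level. If the collector changes between visits, or drifts, the difference between the two shifts remains.

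**4. Which of these applies?** The Abstract and Discussion define the primary outcomes as changes in mean score, which points to step 3. The between-arm tests under Statistical analysis do not subtract baseline, which points to steps 1 and 2. The signed-rank test does use the change, but within subjects, so it does not compare the arms.

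**5. If collectors serve both arms.** A collector's shift falls on both arms and the inflation in steps 1 and 2 largely disappears. What remains is the colour code.

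**The case against.** A reader might infer that a collector who stays unaware must serve one arm only, and that interviewer differences therefore cannot be separated from treatment on any of the three primary outcomes. The documents do not support that.

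- **One arm only does not follow.** Being unaware of the colour scheme also fits one person who uses both colours without knowing what they stand for. Data management speaks of an assessor in the singular, and the article does not say who picks the form. Staffing detail may also sit in the standard operating procedures, which are not shown.
- **Inseparability is too strong.** The same measures are taken at week 0, before the intervention, and the outcomes are defined as changes. A constant shift cancels in the change if the same collector sees both visits, and it would tend to show as a baseline difference between the arms.
- **Exposure of the scales is uncertain.** GMAS and GRAS have four fixed responses per item, and RAKAS is multiple-choice with right or wrong scoring. If patients complete them unaided, an interviewer effect is much weaker.
- **The shifts are assumed.** Nothing in the article supports a particular size, and three hospitals make several collectors per arm plausible.

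All of this stands as a limit on the claim. It does not remove the point, because the stated between-arm comparison does not use change, and the article does not say that the same collector sees both visits. The reading that avoids confounding also leaves collectors with a code that follows the arm.

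**Conclusion.** The procedure as written has a weakness under either reading. Collectors or rooms tied to an arm is the more natural reading, but it is an inference. Under it, interviewer differences are mixed with treatment in the same-time-point comparison of the arms. Under the other, the coloured forms weaken the blinding that the article claims.

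The range of about 9% to 60% rests on no true effect, 247 per arm, one collector per arm and a constant shift of 0.05 to 0.20 SD. It applies to the comparison at one time point, not to a between-arm comparison of change seen by the same collector at both visits. The article should be corrected here; nothing in it shows that the results are biased.

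**What to change.** In Randomization and allocation concealment:

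- Use identical, uncoloured forms for both arms, carrying only a study ID. Pooling collectors while keeping yellow and white forms would exchange confounding for a blinding leak.
- Let one pool of collectors see patients of both arms in order of arrival, at weeks 0 and 12, with no collector or room tied to an arm.
- Record the collector ID on every form.

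In Statistical analysis:

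- Compare the arms on change from baseline, or adjusted for baseline. Only the change score removes a constant shift fully. Adjustment with baseline slope b leaves d(1 − b).
- Report collector by arm, and add a sensitivity analysis of each primary outcome with collector as a factor. This works only if collectors saw both arms.

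Trial status says that results are being analysed, so the room procedure can no longer be changed for this trial. What can still be done is to report who collected data in which arm and at which visit, compare the arms on change, and state the limitation if collectors were tied to an arm.

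For the procedure, the cost is plain forms, one ID field and one sensitivity analysis, with no extra staff or visits. The downside is that collectors handle a mixed queue.
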